#### Body image and self-image

Body image is assessed by the 4-item scale of the EORTC breast cancer-specific quality of life questionnaire, the QLQ-BR23. [50] This scale has been shown to have good reliability (Cronbach's alpha > 0.70) when employed in Dutch research settings. We have added two items to assess self-image, i.e. 'Have you been feeling older as a result of your treatment for breast cancer' and 'Did your self-image change as a result of your treatment for breast cancer?'

#### Psychological distress

Psychological distress is assessed with the 14-item Hospital Anxiety and Depression Scale (HADS). [51] The HADS assesses symptoms of mood disturbance, yielding separate scale scores for anxiety and depression, as well as a total score. Numerous studies have applied the HADS to assess distress among breast cancer patients. [52,53] The questionnaire has been validated for use in the Dutch population, [54] showing good psychometric properties (Cronbach's alphas of both the anxiety and depression scales > 0.79).

#### Generic health-related quality of life

The MOS SF-36 Item Health Survey (SF-36) [55] is used to assess generic health related quality of life. This 36-item questionnaire is organized into 8 multi-item scales assessing physical functioning, role functioning-physical, role functioning-emotional, pain, vitality, social functioning, mental health, and general health perceptions. Summary component scores for physical and mental health can also be calculated. It has been translated, validated and normed in a large number of languages, including Dutch. [56] It has also been used in previous studies of younger patients with breast cancer. [14] We have added one item to assess quality of sleep in the past month.

#### Compliance

Records are kept of the number of CBT sessions attended. Women are also asked to indicate the frequency and duration of relaxation sessions and other homework assignments. Records are also kept of attendance at the in-hospital exercise program sessions, and compliance with the home-based training is determined on the basis of both self-report and the data registered by the heart rate monitors. The monitors register frequency and duration of exercise, total exercise time in and outside the target zone, average heart rate of total exercise, and calorie expenditure.

Women who do not complete the entire program are asked to indicate the reason(s) for their discontinuation (e.g. illness, lack of motivation, burden, etc.). Every effort is made to obtain a final, post-intervention assessment for patients who discontinue the program. This facilitates a maximum sample size for the primary, intention-to-treat analysis. Additionally, all women, including those in the control group, are asked if, during the period of the study, they had pursued any (other) activities relating to their menopausal symptoms (e.g. alternative remedies).

#### Patients' evaluation of the intervention program

At the 12 week evaluation point, women in the 3 intervention arms of the study are asked to complete a brief series of questions about the perceived efficacy of and satisfaction with the intervention program, whether they would suggest any changes to the program, and if they would recommend it to other women experiencing symptoms of premature menopause.

### Statistical analyses

Analysis will first be performed to evaluate the comparability of the intervention and control groups at baseline in terms of sociodemographic and clinical characteristics. Student's t-test or appropriate non-parametric statistics will be used, depending on the level of measurement. If, despite the stratified randomization procedures, the groups are found not to be comparable on one or more background variables, those variables will be employed routinely as covariates in subsequent analyses.

Scores for the FACT-ES, the Hot Flush Rating Scale, the BFLUTS, the SAQ, the QLQ-BR23 body image scale, the HADS, and the SF-36 will be calculated according to published scoring algorithms. Between-group differences over time in mean scores will be tested using a two factor (group × time) multivariate analysis of variance with repeated measures on the time factor. Effect sizes will be calculated using standard statistical procedures. All analysis will, to as great an extent as possible, be conducted on an intention-to-treat basis. In addition, we will perform per-protocol analyses based on patients who complete the entire intervention. As indicated previously, the FACT-ES and the Hot Flush Rating Scale will be used as the primary study endpoints, and the remaining measures will be considered as secondary endpoints. For the analysis of these latter variables, appropriate statistical (p-value) adjustments will be made for multiple testing.

Supplementary analyses will be carried out in which data relating to compliance with the program elements is taken into account. Specifically, we will determine whether the level of compliance (based on attendance records, self-report data and, in the case of physical exercise, data stored in the heart rate monitor) is associated significantly with the changes over time in symptom relief, sexuality, body image, psychological distress, and health related quality of life.

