## Background

Breast cancer is the most common cancer among women in the Netherlands, with an incidence of 71 per 100.000 person years, and a lifetime risk of 10%. [1] Nearly 25% of all women with breast cancer are premenopausal at the time of diagnosis. [2] Ovarian damage is the most significant long-term sequela of chemotherapy and/or endocrine treatment in premenopausal women. [3,4] It can lead to an earlier onset of menopause, with age and duration of treatment being its strongest predictors. [5] Premature menopause is a major concern of younger women undergoing adjuvant therapy for breast cancer [6], as effective and safe treatment options are not currently available.

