### Sample size

The FACT-ES scale, assessing endocrine symptoms [41] is the primary outcome on which sample size calculations are based. Specifically, mean group differences in the FACT-ES scores at 12 weeks and 6 months follow-up, controlling for baseline value, will serve as the primary endpoint of the study. With a total sample of 260 women (65 per group), and under the assumption of no interaction, the study will have 90% power to detect an effect size of 0.4 for the main effects of CBT (n = 130) and physical exercise (n = 130), with the p-value set at 0.05. If the combined effects of CBT and physical exercise are cumulative, or if the effect of CBT varies as a function of exposure to exercise or vice versa, (i.e. there is a significant interaction between CBT and exercise), this number of patients will allow testing each of the 4 cells in the factorial design (group A, B, AB and control group) separately with 80% power to detect an effect size of 0.5, again with p-value set at 0.05. [42]

We will recruit 325 women into the study, to allow for an attrition rate of approximately 20% (i.e. women who discontinue participation in the study entirely, including failure to complete all follow-up questionnaires; those women who discontinue participation in one of the groups but complete the follow-up assessments will be included in the analysis). Thus, 260 women will be available for the primary intention-to-treat analysis.

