### Recruitment and randomisation

The patients are recruited from hospitals in the Amsterdam region. Potentially eligible patients are identified through hospital registries, for the 5-years retrospective inclusion, and through treating physicians, for the 2-years prospective inclusion. They are sent a letter signed by their physician informing them of the study and, if initially interested, asking them to complete a brief questionnaire to screen for menopausal symptoms. If they have no further interest in the study, they are asked to complete a postcard indicating reasons for not participating. In case of no response to the questionnaire or the postcard, a reminder is sent two weeks after the first mailing.

Those women who meet criteria for study entry based on their questionnaire responses are contacted by telephone to provide additional information on the study and to confirm their eligibility. In addition, they receive an extensive baseline questionnaire and informed consent form by mail. Computerized randomization takes place after response to both this baseline assessment and the informed consent. Block randomisation is used to ensure that each intervention consists of equally sized groups. In view of the nature of the interventions, blinding of the participants and the researchers is not possible.

During the follow-up period, self-administered questionnaires are sent to the patients at 12 weeks (T1) and 6 months (T2) post-study entry. Upon completion of the study, women assigned to the control group will be given the choice of undergoing either the CBT or physical exercise program.

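### Background covariates are selected by baseline significance tests, so chance rather than prognostic value decides the adjustment, and the stratification this rule relies on is not described where randomisation is set out

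*Protocol article*

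**What the plan says.** All references are to the protocol article.

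- **Statistical analyses, baseline comparison.** The groups are compared on sociodemographic and clinical characteristics: "Student's t-test or appropriate non-parametric statistics will be used, depending on the level of measurement".
- **Statistical analyses, covariate rule.** The condition opens "If, despite the stratified randomization procedures", and the rule is that, where the groups are "found not to be comparable on one or more background variables, those variables will be employed routinely as covariates" in the analyses that follow. No other rule for background covariates is given.
- **Statistical analyses, model.** Group differences over time are tested by a "two factor (group × time) multivariate analysis of variance with repeated measures on the time factor". Both the FACT-ES and the Hot Flush Rating Scale are called primary here.
- **Recruitment and randomisation.** Allocation is computerised and takes place after the baseline questionnaire is returned. On the method it says: "Block randomisation is used to ensure that each intervention consists of equally sized groups". No strata are mentioned there or elsewhere.
- **Sample size.** The primary endpoint is "mean group differences in the FACT-ES scores at 12 weeks and 6 months follow-up, controlling for baseline value". This control for baseline is unconditional, but it is stated for the FACT-ES only.

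**The concern.** A significance test of baseline differences between randomised groups tests a null hypothesis that is true by construction. Its result says nothing about whether a variable predicts outcome, and that is the property that makes adjustment worthwhile. Using it as the gate means that two correctly run copies of this trial could end with different models for the same endpoint, and that a strongly prognostic variable would usually stay out.

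The rule also works against stratification. If allocation was stratified, the factors are balanced by design, so they are the variables least likely to be flagged. Yet they are the ones the analysis should carry, because leaving them out makes the standard errors too large.

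At stake are precision and a model fixed in advance. The two descriptions of the randomisation also leave the reader unable to tell which factors, if any, belong in the model.

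**Working it through.** **1. The plan's own figures.** The article gives no figure for the covariate rule, so I first checked the sample size, which assumes no covariate gain. Two-sided 5% is assumed, since sidedness is not stated.
- Main effects, 130 against 130, effect 0.4 SD: 0.4 × √(130/2) − 1.96 = 3.225 − 1.960 = 1.265, which gives power of 89.7% (stated 90%).
- Single cells, 65 against 65, effect 0.5 SD: 0.5 × √(65/2) − 1.96 = 2.850 − 1.960 = 0.890, which gives 81.3% (stated 80%).
- Recruitment: 260 / 0.80 = 325, as stated.

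These figures reproduce, and the covariate rule does not affect them.

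**2. How often the rule fires by chance.** The opening of Study measures lists about 16 baseline items: age, education, marital status, work status, weight, height, medication, smoking and physical activity (9), plus date of diagnosis, tumour characteristics, surgery, reconstruction, radiotherapy, chemotherapy and endocrine treatment (7). The article states no threshold, so I assume 5%, one test per variable, and independence. The chance of at least one flag among k variables is 1 − 0.95^k.

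| k | chance of at least one flag |
|---|---|
| 5 | 23% |
| 10 | 40% |
| 16 | 56% |
| 20 | 64% |

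Any single variable enters about 5% of the time, however prognostic it is.

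A t-test compares two groups and the trial has four. If each active arm were tested against control (simulated with 81 per arm, from 325/4), a single variable would be flagged 12.6% of the time, and the chance of at least one flag would be 49%, 74% and 87% for k = 5, 10 and 15.

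**3. What the rule does to the test.** Simulation of 130 against 130, with 40,000 trials per setting, one covariate with an assumed correlation r with outcome, and no baseline score in the model. The triggered rule adjusts only if the baseline t-test has p < 0.05.

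| r | power at 0.4 SD: never adjusted | triggered | prespecified | type I error: triggered | prespecified |
|---|---|---|---|---|---|
| 0.3 | 89.8% | 90.1% | 92.4% | 4.7% | 4.9% |
| 0.5 | 89.6% | 90.5% | 96.0% | 4.3% | 5.1% |
| 0.7 | 89.3% | 91.1% | 99.4% | 3.7% | 4.9% |

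The triggered rule performs almost like no adjustment. It is conservative because, in the 95% or so of trials where the covariate is not flagged, the unadjusted standard error still includes variation that the covariate would explain.

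**4. Possible gain in precision.** Residual variance is multiplied by 1 − r². At r = 0.3 this is 0.91, a 9% reduction; at r = 0.5 it is 0.75, a 25% reduction. Because baseline FACT-ES is already controlled, r must be read for that outcome as correlation beyond the baseline score. The documents give no value for it.

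**The case against.** Several points on the other side are sound.

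- **Baseline score.** A reader might infer that no covariate enters the primary analysis unless it is imbalanced. The Sample size section contradicts that: baseline FACT-ES is controlled regardless. What remains is that this control is not carried into the model described under Statistical analyses, nor extended to the Hot Flush Rating Scale.
- **Stratification.** A reader might infer that there was none and that the protection referred to does not exist. The documents do not support this. Blocks are commonly used within strata, and an article may leave the factors to the full protocol. The two sections need reconciling; they do not prove an error in the randomisation.
- **Known predictors.** It is tempting to say that strong predictors such as ongoing hormonal therapy or time since chemotherapy are omitted. The article names neither as a predictor of outcome. Background says of earlier menopause that it comes "with age and duration of treatment being its strongest predictors", which concerns onset and not FACT-ES score at follow-up. These variables are left to chance, not excluded.
- **Blinding.** The questionnaire variables are collected before allocation, so lack of blinding cannot change their values.
- **Inputs to the 56%.** Threshold, variable list and independence are assumptions. The 16 items include lifestyle and medication, which may fall outside the tested set, and weight and height are clearly related. Without medication, smoking and activity, 13 remain and 1 − 0.95^13 = 49%.
- **The t-test.** Main effects are two-group contrasts, for which a t-test is usable, so this is minor.

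None of this defends the selection rule itself, which the article states outright and does not leave to a later plan.

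**Conclusion.** The point holds as one of efficiency and prespecification. The adjustment set for background variables depends on chance imbalance: 40% to 64% of correctly randomised trials would trigger at least one covariate for 10 to 20 variables, under the assumed independent 5% tests.

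A reader might go further and infer a false-positive problem or an underpowered trial. The simulations show neither. Type I error under the rule was 3.7% to 4.7%, and power was 90.1% to 91.1%, so the planned 90% is kept. The loss is the additional precision that prespecified covariates would bring. Its size cannot be fixed from the documents: the 9% and 25% variance reductions are illustrations, and the simulated power gains start from a model without baseline score, so they should not be read as gains on top of it.

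The change should be made, because the rule has no statistical merit over a fixed list and replacing it costs little. The mismatch over stratification is a matter of wording, with one consequence for the model: any factors used belong in it.

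**What to change.** 1. Delete the rule that baseline tests select covariates. Describe baseline characteristics by arm, and do not use p-values to choose covariates.
2. Adjust every analysis for a fixed set: the baseline score of the outcome analysed (including the Hot Flush Rating Scale), every stratification factor actually used, and a short list of background variables fixed before unblinded outcome data are analysed. Age is one candidate, since Background names it as a predictor of earlier menopause; the investigators should choose the others on prognostic grounds.
3. State how the baseline score enters the repeated-measures model, so that Statistical analyses matches the endpoint defined under Sample size.
4. Reconcile Recruitment and randomisation with Statistical analyses: name the stratification factors, or remove the word stratified.
5. Add a simple rule for missing covariate values. Study measures says that clinical data are abstracted from medical records only where possible, so a forced covariate could otherwise drop women from the intention-to-treat analysis.

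The cost is a change of wording, a few degrees of freedom, and handling of occasional missing covariates. The sample size does not change.

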## Methods and design

Using a 2 × 2 full-factorial design patients are randomly allocated to one of the four following conditions: CBT, physical exercise, the combination of both interventions or a 'waiting list' control group. The design will allow for testing of the main effect of CBT, the main effect of physical exercise, and the additive or interactive effects of CBT and exercise on menopausal symptoms, the primary outcome measure. Secondary outcomes will include sexual functioning, urinary symptoms, body image and self-image, psychological distress and HRQL. The design of the study and the anticipated flow of the participants are graphically shown in Figure 1. The institutional review boards of all participating hospitals have approved the study. The study is registered at the Netherlands Trial Register (NTR1165) and ClinicalTrials.gov (NCT00582244).

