### Study sample

The study sample will be composed of 325 women, younger than 50 years of age, with histologically confirmed primary breast cancer (stages: T1 – T4, N0 – N1 and M0). All women will have been premenopausal at the time of diagnosis, have completed adjuvant chemotherapy a minimum of 4 months and a maximum of 5 years prior to study entry, and will currently be disease-free. Hormonal therapy can still be ongoing. Potentially eligible women are screened for the presence of at least one of the following 3 menopausal symptoms during the previous week: hot flushes, sweating and/or vaginal dryness. Women are excluded from the study if they lack basic proficiency in Dutch, if they have serious cognitive or psychiatric problems, or serious physical comorbidity that would preclude them from participating in a physical exercise program. Since physical exercise may be contraindicated as a treatment for hot flushes in obese women, [39] patients with a BMI ? 30 are excluded from the study. Patients participating in concurrent studies or rehabilitation programs containing comparable psychosocial interventions are also excluded.

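### The sample size section makes FACT-ES the only primary endpoint, the analysis section makes FACT-ES and the Hot Flush Rating Scale both primary, and p-value adjustment is confined to the secondary endpoints, so there is no familywise error control across the two primary scales.

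*Protocol article*

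**What the plan says.** Two sections of the protocol article define the primary endpoint, and they differ.

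- **Sample size:** "The FACT-ES scale, assessing endocrine symptoms [41] is the primary outcome on which sample size calculations are based". It goes on to say that "mean group differences in the FACT-ES scores at 12 weeks and 6 months follow-up, controlling for baseline value, will serve as the primary endpoint of" this trial. The error level is given "with the p-value set at 0.05". The target is 90% power for main effects of 0.4 (130 v 130) and 80% power for single-cell comparisons of 0.5 (65 per cell), with 260 evaluable and 325 recruited.
- **Methods and design:** the factorial effects are to be tested "on menopausal symptoms, the primary outcome measure", in the singular.
- **Current study:** the leading hypotheses concern overall levels of menopausal symptoms. The Study measures section assigns that construct to FACT-ES and describes the Hot Flush Rating Scale separately, under vasomotor symptoms, without calling it primary.
- **Statistical analyses:** the section refers back to an earlier indication and says that "the FACT-ES and the Hot Flush Rating Scale will be used as the primary study endpoints", with all other measures secondary. It then adds: "For the analysis of these latter variables, appropriate statistical (p-value) adjustments will be made for multiple testing".

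**The concern.** The primary endpoint defines the trial's claim, and here a reader cannot tell whether it is one scale or two. The reference back to an earlier statement leads nowhere, because the only earlier statement naming a primary scale names FACT-ES alone.

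The second difficulty is the scope of the adjustment. The article does not leave multiplicity open: it assigns p-value adjustment to the secondary endpoints. Followed as written, two primary scales are each tested at 0.05, with no split of the error rate, no order of testing and no statement on whether one or both must succeed. Participants and researchers are unblinded and the outcomes are self-reported. Freedom to headline whichever scale is significant is therefore worth closing off in advance.

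**Working it through.** **Inputs.** From the Sample size section: 65 per group, so 130 v 130 at each factorial margin; standardized effects 0.4 (main effects) and 0.5 (single cells); level 0.05; attrition about 20%. Assumed, because the article does not give them: two-sided tests (supported by step 1), the correlation r between the two test statistics, and equal effect sizes on the two scales.

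**Step 1: reproduce the stated power with one endpoint at 0.05.** Power ≈ Φ(d·√(n/2) − z), with z = 1.960.

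- Main effects: 0.4 × √65 = 3.225; Φ(3.225 − 1.960) = 89.7% (t-test 89.5%). Stated: 90%.
- Single cells: 0.5 × √32.5 = 2.850; Φ(2.850 − 1.960) = 81.3% (t-test 80.8%). Stated: 80%.
- One-sided tests would give 94.3% and 88.6%, which do not match.
- Recruitment: 260 / 0.80 = 325, as stated.

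The published figures thus correspond to a single endpoint tested at the full two-sided 0.05.

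**Step 2: two primaries, either one sufficient, one treatment contrast.** Familywise error = 1 − P(|Z1| < 1.960 and |Z2| < 1.960), with (Z1, Z2) bivariate normal with correlation r.

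| r (assumed) | familywise error |
|---|---|
| 0 | 1 − 0.95² = 9.75% |
| 0.3 | 9.5% |
| 0.5 | 9.1% |
| 0.7 | 8.3% |
| 0.9 | 7.0% |

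Whatever the dependence, the bound is 0.05 + 0.05 = 10%.

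**Step 3: two primaries, both required.** The familywise error cannot exceed 5%. Power to succeed on both is below the power on either one. With equal effects and independent statistics it is 0.897² = 80.5% for main effects and 0.813² = 66.2% for single cells. Positive correlation raises both figures, but they stay below 89.7% and 81.3% unless r = 1.

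**Step 4: two primaries at 0.025 each.** The critical value becomes 2.241.

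- Main effects: Φ(3.225 − 2.241) = 83.7% (t-test 83.3%).
- Single cells: Φ(2.850 − 2.241) = 72.9% (t-test 71.9%).
- To restore 90% for main effects: n = 2(2.241 + 1.282)² / 0.4², rounded up to 156 per margin, so 312 evaluable and 312 / 0.80 = 390 recruited.
- To restore 80% for single cells: n = 2(2.241 + 0.842)² / 0.5², rounded up to 77 per cell, so 308 evaluable and 308 / 0.80 = 385 recruited.

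**Step 5: FACT-ES as sole primary.** The calculation is that of step 1, and nothing in the Sample size section changes.

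**The case against.** The best defence is that this is a condensed article and that the rule for combining two primaries is normally left to a fuller document. That stands as far as the missing rule goes: its absence alone would be no finding. It does not remove the contradiction, because the article itself fixes two different primary sets and states which endpoints will be adjusted.

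A second defence is that Methods and design makes menopausal symptoms primary and leaves vasomotor symptoms out of its list of secondary outcomes. That fits the analysis section's classification. It still does not fit the Sample size section, which names one scale and one endpoint.

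It can also be said that each test is held at 0.05. That is correct. What is missing is control across the two scales, and inflation follows only if success on either suffices.

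Several stronger readings are tempting, and the document does not support them:

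- **Separate tests at 12 weeks and 6 months.** A reader might multiply the error further by time point. The analysis section plans a joint group × time repeated-measures analysis, and no separate tests at 0.05 are stated.
- **Every hypothesis counted in one family.** The Current study section implies five pairwise contrasts, but nowhere does the article say that all are tested ungated at 0.05. Counting the two factorial main effects as one family would also give a larger figure. Whether they need joint control is a separate question, which this point does not raise and its fix does not answer.
- **The hot flush scale as an unsuitable, diluted primary.** Candidates will be "screened for the presence of at least one of the following 3 menopausal symptoms during the previous week: hot flushes, sweating and/or vaginal dryness", so some may enter with vaginal dryness alone. The Background prevalence of hot flushes describes breast cancer patients generally, not this symptom-screened sample. The scale also covers night sweats, and the Interventions section makes hot flushes and night sweats the main focus of the CBT. The document gives no basis for sizing any dilution.

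**Conclusion.** The point holds in this form: the article contradicts itself on the primary endpoint and, read as the analysis section stands, provides no familywise control across the two primary scales. For one treatment contrast with either scale sufficient, the error is about 9% instead of 5%; the range rests on the assumed correlation. With both scales required, the error is controlled, but the published power no longer applies and no replacement is given. The power figures for two primaries further assume that the FACT-ES effect sizes carry over to the Hot Flush Rating Scale, for which the article gives none. It would go too far to say that the trial has no error control at all.

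**What to change.** In Statistical analyses, name FACT-ES as the sole primary endpoint, and list the Hot Flush Rating Scale as the first secondary endpoint, inside the family to which the p-value adjustment applies. Remove the reference to an earlier indication. This agrees with the Current study, Methods and design, and Sample size sections, and it leaves 260 evaluable, 325 recruited and 90%/80% power unchanged. The cost is wording only; the downside is that the hot flush scale loses its primary status.

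If both scales are to stay primary, say so in Sample size as well and test each at 0.025. Restate power as about 83% for main effects and about 72% for single cells, with the assumption of equal effect sizes made explicit. Keeping the planned power instead would require about 390 recruited for main effects (about 385 for single cells), as derived above.
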